### Endpoints

2.6

The primary endpoint is the change from baseline in the QMG score at Week 30 after randomization. Secondary endpoints include the assessment of the following variables at Weeks 4, 8, 12, 18, 24, and 30 after randomization: change from baseline in the MG-ADL score; the proportion of patients achieving minimal manifestation status (MMS) (defined as the absence of any functional limitations due to myasthenia, with certain weakness detected by a trained neurologist); the proportion of patients with a reduction of ≥2 points in the MG-ADL score from baseline; the proportion of patients with a reduction of ≥3 points in the QMG score from baseline; changes in the dose of corticosteroids and other immunosuppressive agents at Weeks 24 and 30; the proportion of patients who discontinue corticosteroids and other immunosuppressive agents at Weeks 24 and 30; the proportion of patients on prednisone (or equivalent corticosteroids) ≤5 mg/day at Weeks 24 and 30; the incidence of MG relapse/acute exacerbation and MG crisis at Week 30; and the incidence of AEs and SAEs.

The study will also analyze the PK/PD characteristics of telitacicept in different sequential treatment groups. Blood samples will be collected to measure PK-related indicators before the first administration of telitacicept (30 minutes prior), and at 6, 24, 48, and 72 hours, as well as at Week 1, 4, 8, 12, and 24 (before each dose). The PK parameters to be measured include blood drug concentration, clearance rate, volume of distribution, interindividual variability, and other relevant indicators. Immune globulins will be tested during the screening period, during the first cycle of efgartigimod treatment, prior to the first dose of telitacicept, and at Weeks 1, 4, 8, 12, and every 4 weeks thereafter, until the end of the study. During the screening period, prior to the first dose of telitacicept, and at Weeks 4, 12, and 24 of telitacicept treatment, BLyS/APRIL, B-cell flow cytometry, T-cell flow cytometry, and cytokines such as IL-6 will be assessed, all before dosing.

The evaluation of adverse events will adhere to the NCI-CTCAE V5.0.

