### Study subjects

2.2

The study will enroll patients aged 18–80 years with AChR-Ab-positive gMG, classified as Myasthenia Gravis Foundation of America (MGFA) Class II-IV [15]. Full eligibility criteria are provided in **Table 1**.

**Table 1 T1:** Inclusion and exclusion criteria.

Inclusion criteria
1. Patients must voluntarily sign the informed consent form.
2. Age between 18 and 80 years, inclusive, with no sex restrictions.
3. Diagnosis of MG according to the 2020 Chinese Guidelines for the Diagnosis and Treatment of MG, with serologically confirmed AChR-Ab positivity.
4. Classified as Myasthenia Gravis Foundation of America (MGFA) clinical class II–IV.
5. Patients with fluctuating MG symptoms before enrollment, defined as an MG-ADL score ≥6 or a Quantitative Myasthenia Gravis (QMG) score ≥8, persisting for more than 24 hours.
Exclusion criteria
1. Presence of other active autoimmune diseases, such as systemic lupus erythematosus, rheumatoid arthritis, or Sjögren’s syndrome.
2. Active infections, including herpes zoster, HIV, active tuberculosis, or active hepatitis.
3. Thymoma with a history of surgery within the past six months.
4. History of malignancies other than thymoma.
5. Severe hepatic or renal impairment, defined as ALT or AST >3×ULN, or an estimated glomerular filtration rate (GFR) <30 mL/min/1.73 m².
6. Serum IgG level ≤400 mg/dL.
7. Prior use of biologic agents within five times their elimination half-life, including: Telitacicept within two months prior to enrollment. Efgartigimod within one month prior to enrollment. Rituximab or other targeted biologic therapies within six months prior to enrollment.
8. Use of intravenous immunoglobulin (IVIG) or plasma exchange within two months before enrollment.
9. Receipt of any live vaccine within three months prior to enrollment or planned vaccination during the study period.
10. Pregnant or lactating women and those planning to conceive during the study period.
11. Known hypersensitivity to human-derived biologic products.
12. Participation in any clinical trial within 28 days before enrollment or within five times the elimination half-life of the investigational drug.
13. Other conditions deemed inappropriate for study participation by the investigator (e.g., severe psychiatric disorders).

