### Randomization and intervention

2.3

Randomization will be conducted using a computer-generated random sequence, with all assignments managed through a central randomization system to ensure allocation concealment. Eligible participants will be randomly assigned in a 1:1:1 ratio to one of three groups, with 20 patients per group: E + 1w+T group: Efgartigimod followed by telitacicept with a 1-week interval; E + 2w+T group: Efgartigimod followed by telitacicept with a 2-week interval; T only group: Telitacicept monotherapy. All participants will receive biologic therapy in addition to standard-of-care treatments, which include acetylcholinesterase inhibitors, corticosteroids, and non-steroidal immunosuppressants such as tacrolimus. The study flowchart is shown in **Figure 1**.

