### Statistical method

2.9

This study will analyze data based on the intention-to-treat (ITT) principle. Efficacy will be evaluated based on the full analysis set (FAS), and safety will be evaluated based on the safety analysis set (SS). FAS is defined as all participants who were randomly assigned, received at least one dose of the study drug, and have efficacy evaluations. The safety analysis set is defined as all participants who were randomly assigned, received at least one dose of the study drug, and have safety assessments, summarized by the actual treatment received.

The primary endpoint, the change in QMG score from baseline at 30 weeks, will be compared using ANCOVA for E + 1w+T vs. T only and E + 2w+T vs. T only, adjusting for baseline QMG score. Missing values for the primary endpoint will be handled using the last observation carried forward (LOCF) method. Secondary endpoints will be analyzed according to general statistical principles. Two-sided tests will be used with a significance level of 5%.

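### The MMS endpoint, as defined, scores a participant in full remission as a failure; as a lesser point, the steroid proportions do not exclude participants who cannot show a change

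*Protocol article*

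**What the plan says.** **MMS.** Section 2.6 lists the proportion achieving MMS among the secondary endpoints at Weeks 4 to 30 and gives the definition itself: "defined as the absence of any functional limitations due to myasthenia, with certain weakness detected by a trained neurologist". The closing condition, "with certain weakness detected by a trained neurologist", is part of that definition. It does not mention a better state and lists no separate remission endpoint.

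**Steroid and immunosuppressant endpoints.** The same section lists "the proportion of patients on prednisone (or equivalent corticosteroids) ≤5 mg/day at Weeks 24 and 30" and "the proportion of patients who discontinue corticosteroids and other immunosuppressive agents at Weeks 24 and 30". Neither states a denominator, and the first does not say how a participant on 0 mg is counted. Section 2.9 (Statistical method) gives one general population: "Efficacy will be evaluated based on the full analysis set (FAS"). It names no endpoint-specific subset.

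**Who enters.** None of the five inclusion criteria in Table 1 concerns current steroid or immunosuppressant use. The severity criterion is symptom-based, "defined as an MG-ADL score ≥6 or a Quantitative Myasthenia Gravis (QMG) score ≥8, persisting for more than 24 hours". Section 2.3 (Randomization and intervention) adds the biologics to "standard-of-care treatments, which include acetylcholinesterase inhibitors, corticosteroids, and non-steroidal immunosuppressants such as tacrolimus", which describes the background without saying that every participant takes each class. Participants are "randomly assigned in a 1:1:1 ratio to one of three groups, with 20 patients per group".

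**The concern.** A responder endpoint should count a participant as a success at the target state or anything better. The MMS definition joins two conditions, no limitation and some weakness on examination, and so excludes the best outcome. Whether a participant is misclassified depends on how well he or she has done after randomization, so randomization gives no protection: the arm producing more complete remissions loses more successes.

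The steroid endpoints raise a milder problem of a different kind. A participant who enters at or below 5 mg/day needs no reduction to be at or below 5 mg/day at Week 24 or 30. A participant who enters off a drug class cannot discontinue it. If both stay in the denominator, the proportion mixes baseline status with treatment effect. This matters because the Introduction gives less reliance on steroids and long-term immunosuppression as an aim of the sequential strategy.

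**Working it through.** **The plan's own figure.** The article gives no expected rate for any of these endpoints. Its only size figure concerns the primary endpoint: difference 4, SD 4.3, R² 0.3, two-sided α 0.025, power 80%. The residual SD is 4.3 × √0.7 = 3.60. A noncentral-t calculation with 2n − 3 degrees of freedom gives 17 per group (power 80.7%), and 17 / 0.85 = 20. The stated 17 and 20 reproduce, and nothing below affects them.

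**MMS: size per participant.** 1/20 = 5 percentage points.

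**MMS: illustration.** Every rate here is an assumption. Let p be the true proportion at MMS or better and f the share of those with no detectable weakness. The definition as written counts p(1 − f). Power is for two proportions, 20 per arm, two-sided 5%:

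Φ{ [d − 1.96·√(2p̄(1−p̄)/20)] / √([p₁(1−p₁)+p₂(1−p₂)]/20) }

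Take p = 40% (telitacicept only) and 70% (sequential):

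| f, T only / sequential | Counted | Difference | Power |
|---|---|---|---|
| 0 / 0 | 40% v 70% | 30 points | 48% |
| 10% / 10% | 36% v 63% | 27 points | 40% |
| 30% / 30% | 28% v 49% | 21 points | 27% |
| 10% / 30% | 36% v 49% | 13 points | 13% |
| 10% / 50% | 36% v 35% | −1 point | 3% |

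Starting from 50% v 80%, the last two rows become 11 and −5 points. Equal shares shrink the difference in proportion; unequal shares can erase it.

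**Steroid ≤5 mg/day: illustration.** Let s be the share already at or below 5 mg/day at entry, all counted as successes on the reading that 0 mg qualifies. Let 30% and 60% be the assumed success rates among the rest. The whole-set rate is s + (1 − s)p, so the difference is (1 − s) × 30 points.

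| s | Whole set | Difference | Power, 20 per arm | Power, at-risk only |
|---|---|---|---|---|
| 10% | 37% v 64% | 27 points | 40% | 44% (18 per arm) |
| 30% | 51% v 72% | 21 points | 27% | 35% (14 per arm) |
| 50% | 65% v 80% | 15 points | 18% | 26% (10 per arm) |

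**Noise or bias?** At s = 30%, the SD of the between-arm difference in baseline share is √(2 × 0.3 × 0.7 / 20) = 14.5 points (12.6 and 15.5 at s = 20% and 40%). This is imbalance in baseline status, not in the outcome. With 30% success among the rest in both arms, it passes through at 1 − 0.3 = 0.7, giving 14.5 × 0.7 ≈ 10 points. The usual binomial SD already contains it:

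- total variance: 2 × 0.51 × 0.49 / 20 = 0.0250 (SD 15.8 points);
- from baseline imbalance: 0.7² × 0.021 = 0.0103;
- from outcomes among the rest: 2 × 0.7 × 0.3 × 0.7 / 20 = 0.0147;
- sum: 0.0250.

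The standard test therefore allows for it, and simulated type I error at s = 30% was 4.2% against a nominal 5%.

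**The case against.** **On MMS.** The wording is loose and could describe weakness that may remain. The Introduction and Discussion treat MMS as a level to be reached, and the Discussion names it among the criteria for tapering, which suggests a floor. Full responders also still register in the QMG and MG-ADL changes and in the ≥3-point and ≥2-point responder endpoints. This is fair evidence of what was meant, and it limits the harm. It does not change the definition, which an assessor applying it literally would follow. Because the article states a rule here, this is not detail left to an analysis plan.

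**On steroids.** The objection is stronger. A reader might infer that steroid-free entrants are counted as successes by rule; the article never says so, and requiring participants to be on prednisone could equally exclude 0 mg. That second reading has its own fault, since it would fail those who taper off completely. To discontinue implies prior use, so a user-only denominator is a natural reading of that endpoint. Denominators may also be settled in the full protocol or analysis plan. A reader might further infer that baseline steroid use distorts the arm comparison. It does not: allocation is randomized, so baseline use is balanced in expectation, and what remains is dilution and chance variation.

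**On breadth.** It would be wrong to fault the responder endpoints as a group; the QMG and MG-ADL ones are sound.

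**Conclusion.** The MMS point holds on the text. Read as written, full remission without detectable weakness is a failure, at 5 percentage points per participant in an arm of 20. The total effect is unknown because the documents give no remission rate; the table above shows only how an assumed difference could behave. A reader might conclude that the losses fall mostly in the better arm. That is plausible but rests on no figure in the documents. What can be said is that the error works against whichever arm has more full remissions.

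The steroid point holds only as a lesser one: an unstated rule for 0 mg and an unrestricted denominator, which attenuate the effect by the factor 1 − s and add noise without bias. The share s is not given either.

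All affected items are secondary endpoints in a trial described as exploratory. The definitions are worth correcting, but the trial's main conclusion does not depend on them.

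**What to change.** 1. Define the endpoint as MMS or better: no functional limitation from myasthenia, with or without weakness on examination. This is a wording change with no cost.
2. State that 0 mg counts as ≤5 mg/day.
3. Report the ≤5 mg/day proportion among participants above 5 mg/day at baseline, and each discontinuation proportion among baseline users of that class. These subsets are fixed before treatment, so the randomized comparison within them remains valid. The cost is smaller denominators, about 14 per arm if 30% enter at or below 5 mg/day (assumed), and power stays low either way.

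The article reports that nobody has yet been enrolled. If that still holds, all three can be settled before any data exist, which matters in an open-label trial where definitions chosen later would be hard to defend.

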### Sample size calculation

2.7

Based on previous studies (15), the change in QMG score from baseline at 24 weeks in the monotherapy group was -9.6 (± 4.3). It is assumed that the efficacy of the two sequential treatment regimens in this study will be similar, with a predicted additional 4-point reduction in the QMG score at 30 weeks for the sequential treatment group compared to the monotherapy group (10, 19), with SD = 4.3. Using a two-sided test, α = 0.025, and power = 80%, ANCOVA will be used for pairwise comparisons, assuming R2 = 0.3. The required sample size per group is 17 participants. Considering a 15% dropout rate, 20 participants per group are planned, for a total of 60 participants.

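### The two primary comparisons are sized at 0.025 each, but the analysis section gives only 5% and no multiplicity rule; naming Holm at an overall 5% would settle this and recover power

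*Protocol article*

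**What the plan says.** The planning level is in section 2.7 (Sample size calculation) of the protocol article: "Using a two-sided test, α = 0.025, and power = 80" percent. The same section says that "ANCOVA will be used for pairwise comparisons", "assuming R2 = 0.3". The effect is set "with a predicted additional 4-point reduction in the QMG score at 30 weeks for the sequential treatment group" relative to monotherapy, with SD 4.3. On the two sequential arms it states: "It is assumed that the efficacy of the two sequential treatment regimens in this study will be similar". The result is: "The required sample size per group is 17 participants". Then: "Considering a 15% dropout rate, 20 participants per group are planned, for a total of 60 participants".

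Section 2.9 (Statistical method) has the primary endpoint "compared using ANCOVA for E + 1w+T vs. T only and E + 2w+T vs. T only", adjusted for baseline QMG. The only significance level in that section is a general two-sided 5%. It does not repeat the 0.025 and does not say how the two primary tests share the 5%.

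**The concern.** Two tests against one control arm are planned at one level and, on the page, analysed at another. The reader has two ways to join the sections, and each has a cost.

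- **Each comparison at 5%, as 2.9 reads literally.** The chance of at least one false positive on the primary endpoint is then well above 5%, and the planning level in 2.7 serves no purpose.
- **5% overall, split as 0.025 each, as 2.7 implies.** The error is controlled, but the second comparison is held to 0.025 even after the first has been rejected. The plan assumes that both regimens work about equally well, and in that case this restriction costs the most.

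The Discussion lists the small sample as a limit on power, so power that can be had without more patients matters here.

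**Working it through.** **Inputs, all from section 2.7:** difference 4 points in each sequential arm, SD 4.3, R² = 0.3, two-sided α = 0.025 per comparison, power 80%, 17 evaluable and 20 randomised per arm.

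**1. The plan's own figure.**
- Residual variance = 4.3² × (1 − 0.3) = 12.943, so residual SD = 3.598.
- Normal approximation: n = 2(2.241 + 0.842)² × 12.943 / 4² = 15.4, rounded up to 16.
- Noncentral t with 2n − 3 degrees of freedom: power is 77.8% at n = 16 and 80.7% at n = 17. At n = 17 the noncentrality is 4 / (3.598 × √(2/17)) = 3.24 and the critical t on 31 df is 2.356.
- Dropout: 17 / 0.85 = 20.

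The stated 17 and 20 reproduce.

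**2. Error if each comparison is tested at 5%.** Two independent tests would give 1 − 0.95² = 9.75%. The shared T only arm correlates the tests at about 0.5, which lowers this slightly. In 200,000 simulated trials with no effect in any arm, the family-wise error was 9.1%.

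**3. Flat split against Holm.** Holm tests the smaller p-value at 0.025 and, only if that is rejected, the larger at 0.05. For either comparison:

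P(reject) = P(p₁ ≤ 0.025) + P(0.025 < p₁ ≤ 0.05 and p₂ ≤ 0.025)

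The second term is what the flat split gives up. The results below are from 200,000 simulated trials per scenario, with a random baseline covariate and a separate two-arm ANCOVA for each comparison:

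| Scenario | Measure | 0.025 each | Holm, 5% overall |
|---|---|---|---|
| 17 per arm, both regimens work | per comparison | 79.3% | 84.5% |
| | both shown | 67.6% | 77.9% |
| | at least one shown | 91.1% | 91.1% |
| 20 per arm, both regimens work | per comparison | 86.6% | 90.6% |
| | both shown | 78.1% | 86.0% |
| 17 per arm, only one works | the effective regimen | 79.3% | 79.5% |
| 17 per arm, no effect | family-wise error | 4.7% | 4.7% |

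The 79.3% is below the 80.7% in step 1 because the simulation includes chance baseline imbalance, which the formula ignores.

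Arithmetic check at 17 per arm: the two per-comparison powers must add up to P(at least one) + P(both). Under Holm, (91.1 + 77.9) / 2 = 84.5. Under the flat split, (91.1 + 67.6) / 2 = 79.35. Both agree with the table.

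**4. What one three-arm ANCOVA would add.** At 17 per arm it raises residual degrees of freedom from 31 to 47. With equal residual variances and 0.025 each, power moves from 79.3% to 81.1%. With Holm it moves from 84.5% to 85.7%. So the three-arm model is worth about 1 to 2 points, and the step-down about 5.

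**The case against.** The strongest reply is that nothing here is an arithmetic error. The plan promises 80% per comparison at 0.025, and 17 per group delivers it. The trial calls itself exploratory. A 5% overall level split into two halves is a natural reading of 2.7 and 2.9 together, and sizing at 0.025 is compatible with a later Holm analysis in a statistical analysis plan that is not shown. All of this is fair, and it makes the point a modest one. It does not remove it. The article states two levels for one primary analysis without linking them, and a named rule improves the plan under either reading.

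A second reply is that, taken literally at 5% each, 2.9 already has more power: about 87% per comparison at 17 per arm. That is true, but the price is the 9.1% family-wise error.

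Three stronger readings are tempting, and the document does not support them.

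- **That the plan discards the third arm's data.** Neither section says that separate two-arm models will be fitted. Contrasts from one three-arm ANCOVA fit the wording equally well, and model layout is commonly left to the analysis plan. The control arm is not discarded under either layout.
- **That pooling all three arms is the main source of the gain, and is free.** Step 4 shows that it supplies only a small part. It can also lose power. Suppose, as an assumption, that the other sequential arm has a residual SD 1.3 times that of the two arms compared, and that only the compared regimen works. A pooled three-arm step-down Dunnett test then has 76.1% power, against 80.8% for the two-arm test at 0.025. The protocol gives no arm-specific SDs, so the ratio cannot be checked.
- **That the sample size is wrong.** It is not.

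**Conclusion.** The point holds as a gap between the planning level and the analysis level, together with a testing rule that can be improved. It is not a sample-size error. Left as written, the primary analysis has either a family-wise error of about 9.1% or, at 17 per arm, about 5 points less power per comparison and about 10 points less power to show both effects than it need have. At 20 per arm the losses are about 4 and 8 points.

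These gains rest on the plan's assumption of 4 points in both sequential arms. If only one regimen works, the gain is about 0.2 points. Holm never raises the chance of showing at least one effect. What holds without those assumptions is that Holm rejects whenever the flat split rejects, at the same family-wise level, and requires nothing further about variances.

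**What to change.** In section 2.9, state that E+1w+T versus T only and E+2w+T versus T only will be tested by Holm's procedure at a family-wise two-sided 5%. In section 2.7, add that 0.025 is the first-step level of that procedure. The calculation of 17 per group then stands, because Holm never tests below 0.025.

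The cost is a sentence or two and no extra patients. The article reports that no participants had been enrolled, so the rule can be set before any data exist. One small cost remains: Holm has no simple matching simultaneous confidence intervals, so the text should say which intervals will be reported. Intervals at 97.5% for each contrast would be jointly valid.

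Optionally, say whether the contrasts come from one three-arm ANCOVA or from two-arm fits. If one model is chosen, check that residual spread is similar across arms or use a heteroscedasticity-robust standard error.

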### Data collection and management

2.8

All data will be recorded in an electronic case report form (eCRF) by investigators or clinical research coordinators. Completed CRFs will be submitted to the respective study centers for archiving. All study documents will be considered confidential. The research unit is responsible for maintaining all study materials, including confirmation of all participants (to effectively verify different records, such as research case files), original signed informed consent forms, and detailed records of drug distribution, until 5 years after the completion of the trial. In addition to MG-specific data, participants’ comorbidities and concomitant medications for non-MG-related conditions will be recorded.

